#### Sample Characteristics

Further possible influencing variables including age, medication, or other diseases are recorded chronologically close to baseline assessments. Employees of the care facilities will be asked to complete the health and demographic data questionnaire and the Cumulative Illness Rating Scale [72] for each participant. The questionnaire includes sex, year of birth, diagnosis of dementia, severity of dementia, type of dementia, date of diagnosis, depression, severity of depression, number of medications, medications for dementia, antidepressants, and walking aids. A written consent to collect these data by employees of the care facilities will be obtained from participants or their legal guardian.

### Sample Size

The required sample size was calculated via G*Power version 3.1.9.2 (Heinrich Heine University of Dusseldorf) [73], taking into account the following parameters: analysis of variance (ANOVA) for repeated measures, within-between interaction, small effect size (ɳ²=0.01, d=0.2) [74], 2-sided α-error of .05, power of .80 (1-β), and 2 groups and 2 measurements. The small effect size used for the calculation of required sample size is based on literature review and assumptions of relevant changes for IWD. Previous studies have reported high variation in the effect sizes of the primary outcomes balance, mobility, and gait. In their review, Blankevoort et al [22] reported small negative to large positive effect sizes for balance (d=–0.24 to d=3.59) and functional mobility (d=–0.25 to d=2.37) as well as no to medium effect sizes for normal gait speed (d=–0.11 to d=0.50). These reported variations do not allow determining actual effect sizes. Thus, the magnitude of relevant changes has to be considered to further support the selection of a small effect size. Because dementia is characterized by rapid progression linked to multiple impairments, it is assumed that even small effects are relevant. The calculation of sample size results in a required sample size of 100 participants for each group (total sample size of 200 participants). Considering reasons for dropout, the sample is set to 405 participants.

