### Statistical Analysis

All statistical analysis will be done with SPSS version 23 (IBM Corp). Trained and experienced investigators will evaluate and enter data. Investigators evaluating and entering data are not the same as investigators assessing outcomes. The number of investigators is limited to 2 per assessment method. Prior to actual analysis, interrater reliability (Cohen kappa [76], intraclass correlation coefficient [77]) will be calculated and plausibility (eg, considering range and distribution) will be checked to minimize errors caused by data evaluation and entry.

Because of expected large dropout rate, which can lead to a critical amount of missing data, 2 separate analysis sets are planned: an intention-to-treat analysis and a per-protocol analysis. In the intention-to-treat analysis, all randomized participants regardless of protocol adherence will be included and missing data will be substituted by multiple imputation. Participants with sufficient attendance and adherence to the intervention as well as complete assessments of primary outcomes will be included in the per-protocol analysis, where missing data will not be considered.

Baseline values of participant characteristics will be compared between IG and CG using chi-square tests for categorical data, Mann-Whitney-U tests for nonparametric variables, and *t* tests for continuous and normally distributed parameters. For all normally distributed data (checked by Shapiro-Wilk test), mean and standard deviation will be calculated, and medians and interpercentile ranges will be calculated for not normally distributed data. Treatment effects will be analyzed using 2-factor ANOVA with repeated measurement. A 2-sided *P* value less or equal to .05 will be considered to indicate statistical significance. In addition, 95% confidence intervals and partial Eta² will be calculated. Changes in motor and cognitive function are possible mediators and moderators. These mediating and moderating effects on primary outcomes will be analyzed using multiple linear regression models. Additional explorative data analysis exceeding the proposed planned analyses will be performed. Depending on data structure, adequate analysis methods will be defined. These analyses aim to consider further influencing factors or subgroup analysis as well as the development of forecast models.

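### With 100 analysed per group the trial has 80% power for a between-group difference in change of about 0.4 SD; for the stated d=0.2 power is about 29%

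*Protocol article*

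**What the plan says.** The Sample Size section of the protocol article describes a G*Power calculation for "analysis of variance (ANOVA) for repeated measures, within-between interaction", with a "small effect size (ɳ²=0.01, d=0.2"), and the settings "2-sided α-error of .05, power of .80 (1-β), and 2 groups and 2 measurements". The result is: "The calculation of sample size results in a required sample size of 100 participants for each group (total sample size of 200 participants"). No correlation between the two measurements is given.

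The same section sets the chosen effect against d values from a published review (for normal gait speed, –0.11 to 0.50) and argues that small effects matter in this population. The Dropout section takes 200 as the number to be analysed and raises enrolment to 405 to allow for withdrawal, missing data and poor attendance or adherence. The Statistical Analysis section plans a two-factor repeated-measures ANOVA at the 5% level and adds: "In addition, 95% confidence intervals and partial Eta² will be calculated".

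**The concern.** The article treats eta²=0.01 and d=0.2 as the same effect and uses it for an interaction test. The two agree, through f=d/2, for two independent groups measured once. They do not agree for the difference between groups in change from baseline, which is what this test addresses. If the software was given f=0.10, the trial was sized for an effect twice as large as the d that the article names.

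The design rests on being able to detect a small effect. If it cannot, a non-significant result could be taken as evidence against an effect that the trial was unlikely to find.

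**Working it through.** **Inputs from the Sample Size section.** Two-sided alpha 0.05, power 0.80, 2 groups, m=2 measurements, eta²=0.01 or d=0.2, stated N=200. The pre-post correlation ρ is not given and is treated as unknown.

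**1. Reproducing the stated 200.** The interaction test has noncentrality λ = f²·N·m/(1−ρ), with 1 and N−2 degrees of freedom. Take f = d/2 = 0.10.

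| ρ | Required N (f=0.10) |
|---|---|
| 0 | 396 |
| 0.3 | 278 |
| 0.45 | 218 |
| 0.5 | **200** (power 0.804) |
| 0.55 | 180 |
| 0.7 | 120 |
| 0.8 | 82 |

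Of the values tried, only ρ=0.5 returns 200. At ρ=0.5, λ = 0.01 × 200 × 2/0.5 = 8. Converting eta²=0.01 exactly, f = √(0.01/0.99) = 0.1005, which gives 198.

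**2. What f=0.10 means for an interaction.** Let Δ be the difference between groups in mean change. Once the main effects are removed, the four cell effects are ±Δ/4, so f = Δ/(4·SD). Hence f=0.10 gives Δ = 4 × 0.10 × SD = 0.4 SD. For Δ = 0.2 SD the correct input is f=0.05.

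**3. Independent check by change scores.** With two time points, the interaction test is the two-sample t test on change. The SD of change is SD·√(2(1−ρ)), which equals SD at ρ=0.5. With n per group the t-test noncentrality is (Δ/SD of change)·√(n/2). At n=100:

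- Δ = 0.4 SD: 0.4 × √50 = 2.83 (squared, 8, as in step 1); power 0.804, simulation 0.808.
- Δ = 0.2 SD: 0.2 × √50 = 1.41 (squared, 2); power 0.291, simulation 0.287.
- Difference detectable with 80% power: 0.398 SD.
- N for 80% power at Δ = 0.2 SD: 394 per group, 788 in total.

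**4. The partial eta² scale.** At λ=8 and N=200, partial eta² is 8/(8+200) = 0.038. Sizing for a partial eta² of 0.01 needs about 780 analysed.

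**5. Sensitivity to ρ and to the number analysed.** Power for Δ = 0.2 in units of the cross-sectional SD is shown below. The middle column applies the article's 35% loss to 270 and 135 (175.5 and 87.75). The last column is all 405 at 2:1 with complete data.

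| ρ | 100/100 | about 175/88 | 270/135 |
|---|---|---|---|
| 0 | 17% | 19% | 27% |
| 0.3 | 22% | 25% | 36% |
| 0.5 | 29% | 33% | 47% |
| 0.7 | 44% | 50% | 69% |
| 0.8 | 60% | 67% | 85% |
| 0.875 | 80% | 86% | 97% |

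If d is in units of the SD of change, the ρ=0.5 row applies whatever the true correlation is.

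**The case against.** The article defines neither the correlation nor the standardiser of d. The value 0.5 is back-calculated; it describes what was probably entered, not how the balance, mobility and gait measures correlate over 16 weeks. If they correlate strongly and d is in baseline-SD units, power for 0.2 is well above 29%. At ρ=0.8, all 405 with complete data would give 85%, and the intention-to-treat analysis does include everyone randomised. The 200 follows from f=0.10 and ρ=0.5, so the defect is one of effect-size conversion, not of calculation. The article writes eta², not partial eta², in the sample-size text. Confidence intervals are already planned, and nothing says that a null result will be read as excluding a small effect.

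Much of this stands as a condition on the size of the shortfall. The 29% should be quoted with its assumption, the correlation should be requested rather than asserted, and the partial eta² comparison is only supporting. It does not rescue the claim. Had a correlation of 0.875 been assumed, the same calculation with f=0.10 would have returned about 52, not 200. The 405 are enrolled to leave 100 per group, the article itself expects 35% loss, and multiple imputation does not recreate the lost information, so the last column in the table is an upper bound. The article justifies its effect against published d values; on that scale 0.4 lies near the top of the quoted gait-speed range.

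**Conclusion.** The concern holds. The stated sample size gives 80% power for a difference in change of about 0.4 SD, twice the stated d=0.2. At 100 per group, power for d=0.2 is about 29%, on one of two readings: d in units of the SD of change (any correlation), or d in cross-sectional SD units with correlation 0.5, the value that reproduces the article's own figure. In cross-sectional units 80% power at 200 would need a correlation of about 0.875, which the article neither states nor uses. The power claim is wrong as written and should be corrected, because the case for the design rests on detecting small effects.

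**What to change.** In the Sample Size section, state the correlation that was entered and what d is standardised by. If the sponsor confirms a correlation of 0.5, wording such as this would serve: *With 100 analysed per group, two-sided alpha 0.05 and a pre-post correlation of 0.5, the trial has 80% power for a between-group difference in change of 0.40 SD (f=0.10; partial eta² about 0.04). Power for a difference of 0.2 SD is about 29%.* Add power at 0.2 SD for a few plausible correlations.

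Remove the statement that the trial is powered for d=0.2. Add that a non-significant result will be interpreted by whether the planned 95% confidence interval for the difference in change excludes effects considered relevant.

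The cost is a change of wording and a less favourable stated power. Enrolment, allocation and the planned test stay as they are.

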### Dropout

We assume 3 reasons for dropout: (1) withdrawal from the study, (2) missing data, and (3) low attendance or adherence to MEP. Possible reasons for withdrawal are death, hospitalization, serious deterioration in state of health, refusal to participate, etc. Based on the literature review of Blankevoort et al [22], a dropout rate of 20% caused by withdrawal is expected. Missing data occur if participants are not able to complete the entire test battery because of motivational aspects or multiple motor and cognitive impairments. In addition, some participants will not participate at all in postassessments because of illness or other appointments. We assume a missing data rate of 15%. A total target number of 200 participants (100 per group) for the analysis and an assumed dropout rate (withdrawal and missing data) of 35% requires enrolling 270 participants into the study. Unfortunately, attendance and adherence are often not stated in previous studies [26]. Hence, we decided to double the sample of IG to ensure the required sample of 100 participants in this group. Low attendance and adherence may be caused by illness, motivation, other appointments, disinterest, or other reasons. Hence, a total sample size of 405 participants is required.

All participants will be asked at least twice if they are willing to participate in the assessments to reduce missing data. A familiar caregiver is asked to invite the participant if appropriate. If participants are not willing to complete all measures they are offered to choose assessments they are willing to complete. Moreover, all possible participants will be included in the data collection regardless of whether they discontinued or deviate from the intervention protocol. Caregivers will be asked to support the participants to get to training sessions to improve attendance. If participants miss a session, they are personally invited to the next training session.

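### The dropout allowance multiplies by 1.35 instead of dividing by 0.65, so 405 enrolled leaves about 88 to 92 controls with complete data, not the required 100

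*Protocol article*

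**What the plan says.** The Sample Size section of the protocol article derives a "required sample size of 100 participants for each group (total sample size of 200 participants") from a repeated-measures ANOVA interaction with η² = 0.01 (d = 0.2), two-sided α of 0.05 and power of 0.80. It then adds: "Considering reasons for dropout, the sample is set to 405 participants".

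The Dropout section gives the steps from 200 to 405:

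- The target is set after losses: "A total target number of 200 participants (100 per group) for the analysis".
- Withdrawal: "a dropout rate of 20% caused by withdrawal is expected".
- Missing data: "We assume a missing data rate of 15" per cent.
- The two rates are added, and "an assumed dropout rate (withdrawal and missing data) of 35% requires enrolling 270 participants into the study".
- For low attendance or adherence, only the intervention group is enlarged: "Hence, we decided to double the sample of IG to ensure the required sample of 100 participants in this group".
- The result: "Hence, a total sample size of 405 participants is required".

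The Study Design and Allocation sections give a 2:1 ratio, so 405 means 270 intervention and 135 control participants. The Statistical Analysis section plans an intention-to-treat set (all randomized, multiple imputation) and a per-protocol set (sufficient attendance and adherence, complete primary outcomes, no imputation).

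**The concern.** A dropout rate is a share of the people enrolled. To finish with 200 after losing 35%, one divides 200 by 0.65. Adding 35% of 200 to 200 always gives too few, and the gap widens with the loss rate; at 35% it is large enough to matter.

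The control group is the exposed one. The intervention group is doubled afterwards, so the shortfall there is covered unless many participants are excluded for poor attendance. Controls get no second allowance, because attendance at the exercise program does not apply to them. The plan therefore misses its own per-group requirement under its own assumptions, in the paragraph that justifies the trial's headline sample size. A reader who trusts that paragraph will expect 100 controls with complete data.

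**Working it through.** **Inputs from the protocol.** Target 100 per group, 200 in total; withdrawal 20%; missing data 15%; combined loss 35%; intervention group doubled; total 405; two-sided α 0.05, power 0.80, two groups, two measurements; d = 0.2, that is f = 0.1.

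**Input not in the protocol.** The pre-post correlation. I assume 0.5.

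**1. The plan's own figures.**
- 200 × 1.35 = 270; per group 100 × 1.35 = 135.
- 135 control + 2 × 135 intervention = 135 + 270 = 405.

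Both stated totals are matched exactly, but only by multiplication. The base of 200 also reproduces. With noncentrality λ = N·f²·m/(1 − ρ) = 200 × 0.01 × 2/0.5 = 8, power is 0.804.

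**2. What the 1:1 step yields.**
- 270 × 0.65 = 175.5, not 200.
- Sequential losses: retention 0.80 × 0.85 = 0.68, and 270 × 0.68 = 183.6.
- 270 gives 200 only if the loss is 1 − 200/270 = 25.9%, a rate the plan does not use.

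**3. What the target needs.**

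| Loss model | Total at 1:1 | Per group | After doubling the intervention group |
|---|---|---|---|
| Plan (× 1.35) | 270 | 135 | 405 |
| Additive, ÷ 0.65 | 307.7 → 308 | 154 | 154 + 308 = 462 |
| Sequential, ÷ 0.68 | 294.1 → 295 | 147.1 → 148 | 148 + 296 = 444 |

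**4. What 405 delivers with complete data, before adherence exclusions.**
- Controls: 135 × 0.65 = 87.75, about 88; sequential 135 × 0.68 = 91.8, about 92.
- Intervention: 270 × 0.65 = 175.5; sequential 270 × 0.68 = 183.6.

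**5. Power.** With unequal groups, the equivalent balanced total is N′ = 4·n₁·n₂/(n₁ + n₂), used in place of N in λ, with n₁ + n₂ − 2 error degrees of freedom. At ρ = 0.5, f = 0.1 equals a between-group difference in change of 0.4 SD: a two-sample comparison with 100 per group has λ = 0.4² × 100 × 100/200 = 8, as in step 1.

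| Controls | Intervention | N′ | Power |
|---|---|---|---|
| 100 | 100 | 200 | 80.4% |
| 88 | 100 | 187 | 77.7% |
| 88 | 116 | 200 | 80.4% |
| 88 | 175 | 234 | 86.2% |
| 92 | 100 | 192 | 78.7% |

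With 88 controls, the planned power is kept when about 116 of 175 intervention completers (116/175 = 66%) count as adherent. It falls to 78% when only 100 do (100/175 = 57%). Because every row is set against the effect that 100 per group detects with 80% power, the comparison between rows does not hinge on the assumed correlation; the translation into 0.4 SD does.

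**The case against.** **Power may be intact.** A reader might infer from the missing controls that the trial does not deliver its stated power. The document does not support that. The doubled intervention group offsets the control shortfall over much of the range, and with most of that group retained, power exceeds 80%. The 78% figure needs about 43% of intervention completers to be excluded for poor attendance or adherence, and the protocol states no adherence rate. Equal groups of 88 are not an outcome that the plan describes. This objection stands and limits the point.

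**The intention-to-treat set keeps everyone.** All 135 controls enter that analysis through multiple imputation, so the count of 88 does not apply to it. This also stands. Imputation does not fully restore the information lost with an absent postassessment, however, and the Dropout section sets its target after withdrawal and missing data.

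**88 may be pessimistic.** The 15% includes people who cannot finish the whole test battery, while the per-protocol set needs only complete primary outcomes. Some of those counted as missing could still be analysed. The protocol does not say how many, so this is a reason for caution, not a correction. Nor does it rescue 270, which is presented as following from the full 35%.

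**Practical effect.** The slip biases no estimate and leaves the type I error alone. That is true, and it is why rewording is enough.

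**Conclusion.** The arithmetic is wrong as written, and the document alone shows it. The inflated total should be 308 (295 with sequential losses), not 270. The 405 inherits the error. On the plan's own loss rates, about 88 controls (92 if sequential) have complete data against a requirement of 100, which is 12 or 8 short.

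This conclusion is about the count of controls in the complete-case or per-protocol set. It rests on the stated loss rates applying equally to both groups and on the whole 15% being lost to the primary analysis. The effect on power is conditional: from about 3 points below the planned 80% to about 6 above it, depending on intervention adherence. Those figures use f = 0.1; expressing it as 0.4 SD of change also needs the assumed correlation of 0.5.

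**What to change.** In the Dropout section:

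1. Replace the inflation step with division: 200/0.65 = 308, or 200/(0.80 × 0.85), rounded up to 295, if the losses are meant to act in sequence. Say which is meant.
2. Keep 405 as the enrolment figure, but remove the implication that it secures 100 analysable controls. State that it yields about 88 to 92 controls and up to about 175 to 184 intervention participants with complete data, before adherence exclusions.
3. Say that these counts apply to the complete-case or per-protocol set, and that the intention-to-treat set includes all 135 controls by multiple imputation.

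In the Sample Size section, restate power conditional on intervention adherence. With 88 controls it is about 78% if 100 intervention participants remain, 80% at about 116 and 86% at 175. Declare the pre-post correlation of 0.5 as an assumption, and explain that the 0.4 SD difference in change is its translation of the stated d = 0.2, so that the two figures do not appear to conflict.

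The cost is a change of wording and a less tidy justification. No extra participants and no change to design or analysis are needed.

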### Challenges

There are several challenges in performing intervention studies in IWD. These are related to the selected study design as well as its target group and thus cannot be avoided. However, it is important to deal with these challenges to minimize their impact.

A big challenge in performing intervention studies with IWD is maintaining blinding to group allocation. Although all investigators will be blinded to group allocation, there is a potential risk that participants will disclose their group allocation during assessments. To minimize this risk, investigators will be asked not to talk about the intervention during assessments.

Working with IWD entails several general challenges as they are often suffering from frailty and multimorbidity. According to different motor and cognitive impairments in IWD, it is not possible to develop an intervention completely suitable for all participants. Hence, some adaptions of the intervention cannot be avoided. However, instructors are asked to minimize such adaptions and adhere to the manual as strictly as possible. Besides this, IWD are vulnerable in relation to attendance, adherence, and missing data. For instance, multiple motor and cognitive impairments partially prevent IWD from participating in all subassessments. Thus, attempts to enhance attendance and adherence as personal communication, support, or repeated invitation are planned.

Further challenges are seen in cooperation with care facilities. Employees assume important responsibilities, such as suggesting potential participants, assessing ADL and state of health, or supporting assessments and intervention. Restricted time or missing expertise is a potential risk for limitations. To reduce such limitations, employees will be provided detailed information on how to report required data and support for further problems.

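### The rule for participants who will not do the whole battery gives the primary tests no priority, so balance, mobility or gait data may be lost avoidably while secondary tests are done

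*Protocol article*

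**What the plan says.** The Dropout section of the protocol article lists steps meant to limit missing data. Participants are asked more than once, a familiar caregiver may do the inviting, and people who stop or deviate from the intervention are still assessed. Among these steps stands the rule for partial completers: "If participants are not willing to complete all measures they are offered to choose assessments they are willing to complete". No outcome is exempted or ranked.

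On causes, the same section says: "Missing data occur if participants are not able to complete the entire test battery because of motivational aspects or multiple motor and cognitive impairments". It adds that some people will not attend the postassessment at all. The Challenges section repeats the first cause: "multiple motor and cognitive impairments partially prevent IWD from participating in all subassessments". The rate is given once, without a split by cause, outcome or group: "We assume a missing data rate of 15"%.

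Four other sections bear on the point:

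- **Outcomes (Table 2):** balance, mobility and gait are primary. Strength, lower-limb function, activities of daily living (ADL) and cognition are secondary.
- **Statistical Analysis:** the intention-to-treat set uses multiple imputation. The per-protocol set admits only people with a full set of primary measurements.
- **Participants and Allocation:** an MMSE of 10 to 24 is an inclusion criterion, and MMSE and the modified chair-stand test are minimization factors.
- **Determination of Outcomes:** investigators follow a detailed testing manual, and Multimedia Appendix 2 describes each assessment. Neither is shown.

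**The concern.** The trial stands or falls on balance, mobility and gait, yet the one stated rule for a partly willing participant treats a clock drawing and a Timed Up and Go as interchangeable. Three consequences follow if primary tests are among those dropped.

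- Data for the primary comparison are lost that a different order of offering might have kept.
- The loss may be related to the outcome. Motor impairment is a stated cause of incomplete batteries, and motor performance is what the primary tests measure. Participants are not blinded, so willingness could also differ by group. Imputation in its usual missing-at-random form would then leave some bias.
- A single declined primary test excludes the person from the per-protocol analysis, however many other tests were done.

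**Working it through.** **1. The plan's own figures.** The Sample Size section uses a repeated-measures ANOVA interaction with a small effect (η² = 0.01, d = 0.2, so f = 0.10) and "2-sided α-error of .05, power of .80 (1-β), and 2 groups and 2 measurements". The correlation between the two measurements is not given. Taking ρ = 0.5 (an assumption), the noncentrality is λ = f²·N·m/(1−ρ) = 0.01 × 200 × 2/0.5 = 8. Power is then 0.804, which reproduces N = 200. Other values of ρ do not: 0.3 needs 278 and 0.7 needs 120. Enrolment follows as 200 × 1.35 = 270, or 135 per group, and doubling the intervention group gives 135 + 270 = 405. A priority rule changes none of these figures. It affects only how much primary data survives.

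**2. Slack.** With "a dropout rate of 20% caused by withdrawal is expected" plus 15% missing data, 35% is lost in total. The control group falls to 135 × 0.65 = 87.75, below the 100 required. The intervention group falls to 270 × 0.65 = 175.5. On the same ρ, power is 0.86 if all of those count and 0.78 if only 100 intervention participants are adherent. Primary data in the control group are therefore worth protecting.

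**3. Counting the tests (Table 2).** There are 6 direct primary tests: FICSIT-4, Timed Up and Go, 6-meter walk and three GAITRite walks. There are 11 direct secondary tests: chair-stand, short physical performance battery, E-ADL-Test, 7-item physical performance test, MMSE, animal fluency, S-words, Trail Making Test A, California Verbal Learning Test, digit span and clock drawing. The Barthel Index is completed by staff and left out. Total: 17.

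**4. Illustrative loss per primary test.** 15% of 405 is 60.75, about 61 people. Suppose all of them are partial completers who do about half of the 17 tests, chosen at random. Each primary test is then missing in about 60.75/2 = 30.4 of them, and 30.4/405 = 7.5%. If the 6 primary tests come first and are accepted, they fit within the 8 or 9 tests done, and almost none is missing.

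Let q be the share of the 15% who are partial completers and not wholly absent. Let a be the share of their skipped primary tests that would be done if offered first. Avoidable loss = 15% × ½ × q × a:

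| q | a | Percentage points per primary test |
|---|---|---|
| 0 | any | 0 |
| 0.5 | 0.5 | 1.9 |
| 0.5 | 1 | 3.75 |
| 1 | 1 | 7.5 |

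The article gives neither q nor a. Random choice is also an assumption. Systematic avoidance of motor tests would raise the loss, but refusal through inability is what reordering recovers least (low a).

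**5. Per-protocol set.** If 8 of 17 tests are chosen at random, the chance that all 6 primary tests are among them is C(11,2)/C(17,8) = 55/24,310 = 0.2%. For 9 of 17 it is C(11,3)/C(17,9) = 165/24,310 = 0.7%. Almost every such participant leaves the set. The upper bound is again about 61 people.

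**6. Possible bias, on assumptions outside the article.** Suppose the lowest part of a willingness scale is lost, that this scale correlates r = 0.2 to 0.5 with change, and that 15% is missing overall. The shift in a group's observed mean is r·φ(z_p)/(1−p), where p is the fraction lost in that group. Equal loss in both groups gives no net bias. Losses from 12.5% intervention / 20% control to 10% / 25%, or from 17.5% / 10% to 20% / 5%, shift the difference by about 0.02 to 0.12 SD of change, in either direction. The design difference is 0.4 SD of change (100 per group: 50 × 0.4² = 8 = λ).

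**The case against.** A reader might infer that primary tests will be the ones dropped, that people will drop them because they feel unable, and that the rule itself produces the 15%. The article supports none of this. It speaks of willingness and names motivation as well as impairment, and cognitive tests may be declined just as readily. The rule applies only to people who already refuse the full battery, where the alternative may be no data. It is presented as a way to save data.

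Other objections also carry weight:

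- The 15% includes total non-attendance, so the benefit may be zero.
- Completed secondary tests can inform the imputation. The short physical performance battery contains standing balance and gait speed. It is therefore too strong to say that imputation cannot repair the loss.
- Refusals that reflect inability will not be recovered by reordering.
- Unequal loss between groups is possible but nowhere stated, and without it the illustration gives no net bias.
- Putting six motor tests ahead of everything at baseline could displace measurements needed to enrol and allocate.

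The unseen testing manual may set a running order, but that answers less. An order alone does not cancel an explicit offer to choose. If the manual does protect the primary tests, the sentence in the Dropout section should say so.

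**Conclusion.** This is a stated procedure that can be improved cheaply, not an error that undermines the trial. As written, the rule permits primary data to be lost while secondary tests are completed. The article's own account of causes makes it plausible that some of this loss is not at random and only partly corrected by imputation. One missed primary test costs a participant's place in the per-protocol set.

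The size is unknown. The range of 0 to about 7.5 percentage points per primary test rests on three assumptions: how much of the 15% is partial completion, that partial completers do half of the 17 tests, and that they choose at random. The gain from reordering is smaller where refusal reflects inability. The bias figures are illustrative and require loss that differs between groups.

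**What to change.** For the assessments still to come, change the rule along these lines: *Anyone who declines the full battery is offered the primary tests first, in a fixed order (FICSIT-4, Timed Up and Go, 6-meter walk, GAITRite single task, GAITRite dual tasks), identical in both groups, and then selects from the rest; any test may be refused.* At baseline, keep MMSE and the modified chair-stand test alongside the primary tests, because eligibility and minimization depend on them. If the testing manual already does this, align the Dropout section with it.

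Enrolment began in May 2015, so the change cannot reach assessments already made. For those, report missing primary tests and the reasons by group, where recorded, and consider a not-at-random sensitivity analysis.

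The cost is one line in the manual and some secondary cognitive and ADL data. In the upper-bound illustration, a partial completer who does 8 or 9 tests with the primary ones first has 2 or 3 left for 11 secondary tests. Each secondary test is then missing in 9/11 or 8/11 of these people, against 9/17 or 8/17 under random choice. Applied to 15% of the sample, that is 12.3% against 7.9%, or 10.9% against 7.1%: about 4 percentage points more missing per secondary test. No larger sample is needed.
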